### **5.3 Other Outcomes of Interest**

- Global hospitalization costs intended as amount billed for each patient's acute hospital stay, assessed through the billing department of each hospital (continuous variable – stratified by site).

### **5.4 Safety Outcomes**

NA

## **6. STUDY DESIGN**

### **6.1 General study design and justification of design**

This will be a multicenter randomized controlled trial assessing prognostic yield of cEEG. While there will be no blinding during the EEG procedure, as this would prove highly impractical in the proposed setting; however, the most important outcomes will be assessed blindly (at 6 month). The study will be carried out in four university hospitals (of the five in Switzerland) and one large regional hospital, located both in the German- and the French-speaking part of the country. An RCT seems the best way to address the primary objective of this study, particularly in terms of minimization of biases.

It is expected to randomize 350 patients over a 2 year-recruiting period. Patients will receive either cEEG or 2 rEEG within the first 48 hours following randomization, and then will be followed up until 6 months after randomization.

### **6.2 Methods of minimising bias**

A randomization stratified by center as well as a blinded assessment of the primary outcome at 6 month will be performed to minimize the bias.

#### **6.2.1. Randomisation**

Randomization (1:1) will be stratified by center and generated using the web-based secuTrial® software. Briefly, randomization by blocks of 4 (2 rEEG and 2 cEEG) will be set up in the system by the data managers of the CTU Lausanne. Using login and password, the local investigator (or his designee) will randomize patients after the eligibility check and just before the intervention by asking the system to provide him/her with a randomization number and intervention allocation. Randomization lists will be kept at the CTU Lausanne during the trial and transferred to the sponsor-coordinating investigator for interim analysis or at the end.

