| Study design:                   | Multicenter, open label, randomized, active controlled trial.                                                                                                                                                                                                                                                                                                                                                                                                                                                                                                                                                                                                                                                                                                                                                                                                                                                                                                                      |

|                                               |                                                                                                                                                                                                                                                                                                                                                                                                                                                                                                                                                                                                                                                                                                                                                                                                                                                                                                                                                                                                                                                                                                                                                         |

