#### **6.2.2. Blinding procedures**

The intervention under investigation will not be blinded however the assessment of the primary outcome at 6 months will be performed by a study team member blinded to the intervention done in the study patients.

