#### Exclusion criteria:

- Clinical and/or electrographic *status epilepticus* < 96h before randomization
- Clinical and/or electrographic seizure < 36h before randomization
- Palliative care situation, in which detection of SE or seizures would not have any impact on the patient's care.
- High likelihood of needing a surgical intervention or an invasive diagnostic procedure within the next 48 hours according to the treating physician (as this would require cEEG removal).

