#### **12.5 Confidentiality, Data Protection**

Data protection and confidentiality will be guaranteed. Direct access to source documents will be permitted for purposes of monitoring (12.3), audits and inspections (12.4).

The sponsor-coordinating investigator and statisticians will have access to protocol, datasets and statistical code during and after the study. All local investigators (and delegated study collaborators) will have access to all study documents (protocol, procedures, source documents and eCRF) during the study.

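### Fixed blocks of 4 within center in an open-label trial let a center that tracks its own sequence know up to one allocation in three beforehand

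*Protocol*

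**What the plan says.** The synopsis describes the trial as "Multicenter, open label, randomized, active controlled trial". On allocation, section 6.2.1 says "Randomization (1:1) will be stratified by center and generated using the web-based secuTrial® software", and then that "randomization by blocks of 4 (2 rEEG and 2 cEEG) will be set up in the system by the data managers of the CTU Lausanne". No other block size, and no variation of block size, is mentioned.

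Under the same section, "the local investigator (or his designee) will randomize patients after the eligibility check and just before the intervention", and the system returns the allocation to that person (also section 7.3). The lists themselves stay at the CTU during the trial.

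Section 6.2.2 says: "The intervention under investigation will not be blinded however the assessment of the primary outcome at 6 months will be performed" by a team member who does not know the allocation. Section 12.5 adds: "All local investigators (and delegated study collaborators) will have access to all study documents (protocol, procedures, source documents and eCRF"), during the study. The block size is therefore open to every site.

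Several entry criteria in section 7.1 call for judgement. The need for an EEG is decided by the treating physician or consulting neurologist. A palliative situation is an exclusion, and so is "High likelihood of needing a surgical intervention or an invasive diagnostic procedure within the next 48 hours according to the treating physician".

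**The concern.** Keeping the list at the CTU hides the list. It does not hide an allocation that follows by subtraction from the ones a center has already received. With two places per arm in each block of 4, the fourth allocation is always known once three have been made. The third and fourth are both known when the first two went to the same arm. Center is the only stratification factor, so each center follows a single sequence and block boundaries are easy to track.

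If the next arm is foreseeable, the judgement-based criteria leave room for a patient to be included or left out with that arm in mind. If such choices were related to prognosis, the arms would differ at baseline in expected mortality. The bias protections listed in section 6.2 are stratification by center, blinded assessment at 6 months and validated scales. The last two protect outcome measurement, and none of the three addresses foreseeing the next allocation.

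**Working it through.** **Inputs.** Block of 4 with two places per arm, 1:1, stratified by center (section 6.2.1); five centers and 350 patients (section 6.1). The observer is a center that knows the block size and has noted its own allocations in order.

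The protocol gives no figure for predictability, so there is none to reproduce. Its sample size does reproduce: 61% versus 75% survival, two-sided 0.05 and power 0.80 give 174 per arm (pooled variance, no continuity correction). This point does not affect it.

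**1. Allocations known with certainty.** The six equally likely blocks are AABB, BBAA, ABAB, ABBA, BAAB and BABA.
- AABB and BBAA: the 3rd and 4th are certain (2 each).
- The other four: only the 4th is certain (1 each).
- Expected number per block = (2×2 + 4×1)/6 = 4/3, so the share is (4/3)/4 = 1/3.
- Over 350 patients: 350/3 = 116.7, about 117.

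**2. Incomplete last blocks.** This needs an assumed split. With 70 patients per center there are 17 full blocks (68 patients) and two patients in an unfinished block, neither of them certain. Per center: 17 × 4/3 = 22.7, or 32.4% of 70. Over five centers: about 113. The 117 is thus an upper figure.

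**3. Best-guess accuracy.** Always guess the arm with more places left. The chance of being right, by position, is 1/2, 2/3, 2/3 and 1. The mean is (1/2 + 2/3 + 2/3 + 1)/4 = 17/24 = 70.8%, against 50% by chance.

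**4. Alternatives.** Fixed sizes are by enumeration. Varied sizes are by simulation: 3,000 runs of 70 patients per center, with an observer who knows the set of sizes and all past allocations.

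| Block sizes | Certain | Best guess right |
|---|---|---|
| Fixed 4 | 33.3% | 70.8% |
| Fixed 6 | 25% | 68.3% |
| Fixed 8 | 20% | 66.6% |
| Varied 4, 6 | 5.6% | 69.1% |
| Varied 4, 6, 8 | 2.2% | 67.8% |

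The same simulation with fixed 4 gives 32.4% and 70.5%, in line with step 2.

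**5. What it could mean for the endpoint (assumption).** The documents give no basis for the amount of selection. Suppose that, among the certain third only, selection made expected mortality differ by d points between the arms. The overall difference would then shift by about d/3. For d from 5 to 15 points, that is 1.7 to 5 points, against the 14 points that the trial is sized to detect (section 11.2). This shows scale only and is not an estimate.

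**The case against.** Foreseeability alone does not bias anything. A center would have to track its sequence, act on it, and do so in a way related to prognosis. A reader might infer that the design biases the primary outcome directly; the protocol supports only that it could. Likewise, 117 of 350 and 71% measure predictability, not bias.

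A reader might also infer that the person who checks eligibility is the person who randomizes. Section 6.2.1 does not say so. It places randomization after the eligibility check without naming who checks, and section 7.1 gives two of the three judgements to the treating physician or consulting neurologist. Only the palliative criterion names no assessor.

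Some provisions narrow the risk:
- Section 9.3 limits screening and enrolment to 5 hours, and section 3.8 says the EEG cannot be postponed to await consent. Holding a patient back for a preferred place is therefore difficult.
- Section 2.7 requires written authorization from a physician outside the study.
- Section 7.2 says all adults who need an EEG and meet no exclusion criterion will be considered.
- Section 11.4 foresees analyses adjusted for potential confounders, and baseline severity and comorbidity are collected.

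These points stand as mitigation. None conceals the next allocation, however, and none stops a patient from being left out. Adjustment reaches only what was measured.

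**Conclusion.** The concern holds as a foreseeable and avoidable weakness in allocation concealment. Up to one third of allocations can be known in advance, and the next arm can be guessed correctly 71% of the time. The one-third figure is exact as a long-run average over complete blocks. It applies to the whole trial only if every center tracks its sequence throughout. The figure of about 113 also rests on an equal split over five centers.

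The mortality comparison could be biased as a result. By how much cannot be derived from the protocol, and nothing in it shows that selection took place. The point contradicts no other passage and leaves the sample size as it is. It is worth changing because the remedy is cheap, but it does not invalidate the design.

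**What to change.** For allocations still to be made, have the CTU generate new lists within center with randomly varying block sizes, for example 4, 6 and 8. In section 6.2.1, replace the stated size with a statement that block sizes vary at random, and record the sizes in a document held only by the CTU.

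The gain is in certainty: about 33% of allocations known beforehand falls to about 2%, even if the set of sizes became known. The gain in guessing is small, from 71% to about 68%, so some better-than-chance guessing remains.

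Costs: a protocol amendment under section 2.10, a rule for blocks that are part-filled at the changeover in each center, and slightly looser balance within a center. Investigators who have read the current text will still know how earlier patients were allocated. The protocol does not show whether recruitment is still open; if it has closed, the change is no longer possible.

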### 11.4 Planned Analyses

#### Analysis of the outcomes

All analyses will be carried out by a professional statistician. At study completion, the two interventional groups will be compared regarding survival at six months as "intention to monitor" (predefined analysis for the primary endpoint) and "per protocol", adjusted for potential confounders (logistic regressions).

Analysis of each secondary endpoint will be also conducted using univariate and multivariate approaches.

For univariate approaches, frequency tables ( $\chi^2$  or Fisher exact tests, as needed), t-test, Mann-Whitney U, and Kaplan-Meier tests will be applied, as needed.

For the multivariate approaches, stepwise logistic regression models will be performed to identify independent outcome predictors among those found to have a  $p < 0.1$  on univariate analyses. Accordingly, risk-prediction models will be set-up and "Goodness-of-fit" of these models will be evaluated using a Hosmer-Lemeshow test to ensure the quality of calibration. Solid predictors will be used to predict survival and functional outcome at six months in a model. To evaluate the performance of these models, sensitivity, specificity, positive predictive value, negative predictive value, unweighted accuracy (using exact binomial 95% CI), area under the Receiver Operating Characteristic (ROC) curve, and reclassification analysis (Net Reclassification Improvement – NRI) will be calculated .

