#### **11.4.2. Primary Analysis**

Analyses of the clinical outcomes at study completion will be performed by the team of PD [name], University Hospital of Basel, delegated by the sponsor-coordinating investigator and using the clinical trial datasets provided by the data management team of the CRC Lausanne according to adequate format requested by the statistics.

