#### **11.4.4. Interim analyses**

An interim analysis of the primary outcome will be performed after recruitment of the first 100 patients: if the difference of 14% in survival at six months between the two arms will be met, the study will be interrupted. This analysis will be conducted by the team of the sponsor-coordinating investigator in Lausanne and using the intermediate clinical trial datasets provided by the data management team of the CRC Lausanne.

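### The randomisation lists go, without restriction to used allocations, to the sponsor-coordinating investigator for an interim run by that investigator's team at a recruiting centre, so concealment can no longer be assured

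*Protocol*

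**What the plan says.** Section 6.2.1 sets up central web allocation, 1:1, stratified by centre, in fixed blocks of four. The local investigator or a designee obtains the allocation after the eligibility check. On custody it says: "Randomization lists will be kept at the CTU Lausanne during the trial", and that they are then "transferred to the sponsor-coordinating investigator for interim analysis or at the end". It does not separate used from unused entries.

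Section 11.4.4 fixes the timing: "An interim analysis of the primary outcome will be performed after recruitment of the first 100 patients". The comparison is of survival at six months between the arms. It also names the analysts: "This analysis will be conducted by the team of the sponsor-coordinating investigator in Lausanne". Section 11.4.2, by contrast, delegates the final clinical analysis to a team in Basel.

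Section 12.5 adds: "The sponsor-coordinating investigator and statisticians will have access to protocol, datasets and statistical code during and after the study".

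Other sections give the setting:
- The intervention is not blinded (6.2.2).
- There is no data safety monitoring committee (1.6).
- The sponsor-coordinating investigator may end the trial on early evidence of benefit or harm (2.9).
- Lausanne is listed among the participating centres (3.2).

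**The concern.** Section 6.2.1 conceals allocation by having the system disclose each assignment only once the patient has been found eligible. The same section then allows the whole list to leave the CTU in mid-trial, for a recipient whose hospital recruits.

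Eligibility leaves room for judgement. Section 7.1 asks whether the treating physician or consulting neurologist sees a need for an EEG. The exclusions in 7.1 ask whether the situation is palliative and whether surgery or an invasive procedure is likely. Someone who knows the next arm can influence who enters, and selection of that kind biases a mortality comparison however well death is ascertained.

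Separately, if a team at a recruiting centre knows the mortality difference between arms, enrolment and care in an open-label trial can shift while the trial runs.

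**Working it through.** **1. Is the interim team at a recruiting centre?** Section 3.2 lists Lausanne, Bern, Basel, Sion and Geneva as the centres. Section 6.1 counts five hospitals. Section 2.6 counts a coordinating investigator plus four local principal investigators. One lead per hospital leaves the coordinating investigator for the fifth. That the Lausanne group enrols is therefore a strong inference, not an explicit statement.

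**2. Can the transferred list hold future allocations?** Section 12.1.2 says that the web system assigns from a randomisation list, so the sequence exists in advance. Section 6.2.1 transfers the lists without restriction. Disclosure of unused entries is the plain reading, but it is still a reading.

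**3. Is recruitment still open at the interim?** No pause is stated. The synopsis gives a study duration of 30 months, which equals 24 months of recruitment plus 6 of follow-up and leaves no room for one.

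**4. How many patients are still to be randomised?** The protocol gives no figure for this. Its sample size, used here only as background, reproduces. With survival of 61% and 75%, mean 68%, two-sided 0.05 and power 0.80:

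n = [1.960 × √(2 × 0.68 × 0.32) + 0.842 × √(0.61 × 0.39 + 0.75 × 0.25)]² / 0.14² = 173.1, so 174 per arm and 348 in total.

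The planned accrual is: "It is expected to randomize 350 patients over a 2 year-recruiting period". Assuming that it is uniform:
- Rate: 350 / 24 = 14.58 per month.
- 100th patient enters: 100 / 14.58 = month 6.86.
- 100th patient reaches six months: 6.86 + 6 = month 12.86.
- Randomised by then: 12.86 × 14.58 = 187.5.
- Remaining: 350 − 187.5 = 162.5, or 46% of 350.

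| When the list moves | Still to be randomised, all sites |
|---|---|
| Once 100 are recruited | 350 − 100 = 250 |
| 100th patient reaches six months | about 163 |
| One month of data cleaning later | 162.5 − 14.58 = about 148 |
| Three months of data cleaning later | 162.5 − 43.75 = about 119 |

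**5. How many of these are at Lausanne?** Accrual by site is not given. If Lausanne took one fifth (equal accrual), the 162.5 would include about 33 of its patients. If it took 40%, about 65. Both shares are assumptions.

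**6. What does the list add to what can already be guessed?** In an open-label centre with known blocks of four, the six possible sequences can be enumerated. Taking the three that begin with A (the others mirror them):
- AABB: assignments fixed by those before them, 2; expected correct guesses 0.5 + 0 + 1 + 1 = 2.5.
- ABAB: fixed, 1; correct 0.5 + 1 + 0.5 + 1 = 3.
- ABBA: fixed, 1; correct 0.5 + 1 + 0.5 + 1 = 3.

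Certain: 4/12 = 33%. Correct under best guessing: 8.5/12 = 71%. With the full list, both become 100%.

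**The case against.** The strongest reply is that the transfer is tied to the interim, which needs only the analysed patients' allocations, so the authors may never have meant to release unused entries. That may be so, but the wording does not confine it. The same fact shows that handing over the lists serves no analytic purpose. This part of the objection limits the claim to concealment not being assured, rather than lost.

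Second, the list goes to one person at one of five centres, while patients are randomised locally. This stands: exposure is direct at Lausanne and conditional elsewhere. A reader might take the 163 as compromised allocations, but it counts everyone randomised after the transfer at all sites.

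Third, death is a hard outcome, assessed blind (9.2.1) and centrally (9.3), and an independent physician must authorise each inclusion (2.7). These limit biased ascertainment, and the authorisation protects the patient's interests. None of them prevents selective enrolment by someone who knows the next arm.

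A reader might also infer that 11.4.4 contradicts the statement in 11.4, "All analyses will be carried out by a professional statistician". The documents do not show this. The Lausanne team may include such a statistician, and the administrative pages that might settle it are not available. Nor does any section say that the individuals who compute the interim are those who enrol or treat. What is documented is a team at a recruiting centre.

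**Conclusion.** The concern holds in this form. As written, 6.2.1 and 11.4.4 together put unrestricted randomisation lists and the interim mortality difference with the sponsor-coordinating investigator's team at a participating centre during recruitment, with no firewall. Concealment can then no longer be assured, directly at Lausanne and elsewhere only if the information is passed on.

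About 163 patients across all sites would still be to be randomised (119 to 250 by timing of the transfer). That is an upper bound on those directly affected at each timing, and it rests on uniform accrual. Fixed blocks of four already leave concealment imperfect, so the list removes what remains.

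This needs correcting before the interim, because concealment cannot be restored after release and the repair is cheap. A claim that concealment is certainly lost for all remaining patients would go beyond the text.

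**What to change.** - **6.2.1:** keep the lists at the CTU until database lock. For the interim, release only the allocations of the patients in that analysis.
- **11.4.4:** have the interim run by a CTU statistician, or by another who takes no part in enrolment, treatment or outcome assessment at any site. That person returns only continue or stop. Moving the work to the team delegated for the final analysis does not by itself meet this condition, because Basel is also a participating centre.
- **12.5:** withhold aggregated outcome comparisons by arm from the sponsor-coordinating investigator and the site investigators until lock. The limit must be on aggregated comparisons: site investigators know their own patients' allocations in this open-label trial and validate the eCRFs (12.2.2).

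The cost is amendment wording. The CTU already holds the lists and manages the eCRF independently (12.1.1), and no committee has to be set up. The downside is that the sponsor's team does not see the interim numbers.
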